#### Covariates-Adjusted Analyses

The primary model (model 1) previously described will be rerun after further adjusting for the following covariates (model 2): economic development level; locality; and other baseline covariates that have shown a significant difference (*P*<.01) between the intervention and control groups in a univariate comparison, including all the baseline variables previously listed (see “Patient Characteristics and Baseline Comparison”).

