### Patient Characteristics and Baseline Comparison

Discrete baseline variables will be summarized by frequencies and percentages. Percentages will be calculated using the number of patients for whom data is available. Continuous variables will be summarized by using mean and SD, and median and interquartile range (Q1-Q3). No adjustment for clustering will be applied when comparing baseline characteristics. Standardized differences between groups in baseline characteristics will be reported. A less than 0.1 standard difference will be used to indicate a negligible difference in the mean or proportion of a baseline variable between treatment groups [14].

Variables for baseline measures will be tabulated, including demographic (age, sex, ethnicity), socioeconomic status (education level, household income, health insurance), anthropometric measurements (weight, BMI, waist circumference, BP), smoking status, diabetic complications, laboratory data (HbA_1c_, FBG, LDL-C, serum creatinine), and score of the summary of diabetes self-care activities.

Cluster characteristics will be summarized in stratified and overall randomization groups. The cluster characteristics at baseline are age of the community or village doctors, smartphone operation system (iOS or Android) that the community or village doctors were using, and number of patients with T2D registered.

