#### Other Variables

The following outcomes will be analyzed using descriptive statistics without any adjustment for clustering.

Concomitant medications. Insulin injection and oral antidiabetic drug intake at baseline and at end-of-study assessments. The combination of different oral antidiabetic drug regimens or the combination of insulin injection and oral antidiabetic drugs, or their single use will also be summarized.New-onset comorbidities and diabetic complications will be described as the numbers and percentages of patients with each new onset complication by treatment groups.Direct medical cost is the self-reported direct cost on medication and medical expense for health care services (inpatient or outpatient cost, medication cost), including total cost and out-of-pocket cost.

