**Self-reported medical history and complications**								
	Duration of diabetes (years), median (Q1, Q3)		xxx (xxx, xxx)		xxx (xxx, xxx)		x.xxx	
	Current smoker, n (%)		xxx (xx.x)		xxx (xx.x)		x.xxx	
	Hypertension, n (%)		xxx (xx.x)		xxx (xx.x)		x.xxx	
	Dyslipidemia, n (%)		xxx (xx.x)		xxx (xx.x)		x.xxx	
	Diabetic nephropathy, n (%)		xxx (xx.x)		xxx (xx.x)		x.xxx	
	Diabetic retinopathy, n (%)		xxx (xx.x)		xxx (xx.x)		x.xxx	
	Peripheral neuropathy, n (%)		xxx (xx.x)		xxx (xx.x)		x.xxx	
	Lower extremity, n (%)		xxx (xx.x)		xxx (xx.x)		x.xxx	
	Macro-vascular, n (%)		xxx (xx.x)		xxx (xx.x)		x.xxx	

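### Model 2 picks extra covariates by a between-arm P<.01 baseline test, which selects chance differences smaller than the plan itself calls negligible and leaves out balanced prognostic variables

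*SAP article*

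**What the plan says.** Under Covariates-Adjusted Analyses, model 2 is the primary model (model 1) with economic development level and locality added, together with "other baseline covariates that have shown a significant difference (*P*<.01) between the intervention and control groups in a univariate comparison". The candidates are described as "including all the baseline variables previously listed (see “Patient Characteristics and Baseline Comparison".

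The section it points to says of the baseline table: "No adjustment for clustering will be applied when comparing baseline characteristics". It reports standardised differences and gives its own yardstick: "A less than 0.1 standard difference will be used to indicate a negligible difference". Its variable list ends with "smoking status, diabetic complications, laboratory data (HbA_1c_, FBG, LDL-C, serum creatinine), and score of the summary of diabetes self-care activities". Neither duration of diabetes nor glucose-lowering treatment is in that list.

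Elsewhere, the Table 1 shell does carry a row for "Duration of diabetes (years), median (Q1, Q3"). Duration is also in the imputation model, in the propensity model and among the five subgroup factors. Baseline treatment appears only under Other Variables, for description: "Insulin injection and oral antidiabetic drug intake at baseline and at end-of-study assessments".

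The Abstract classes the further adjusted models as sensitivity analyses. Model 2 or a similar further adjusted analysis is planned for the primary outcome, the other binary outcomes, the continuous outcomes, hypoglycemia and the self-care scores.

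**The concern.** Participant Recruitment and Randomization states that clusters were randomised once baseline assessments were complete. Allocation therefore could not influence who was enrolled, and any baseline difference between arms is chance. A between-arm test then screens for the size of a chance difference, not for whether the variable predicts HbA1c control. A strongly prognostic variable that is balanced is excluded, and an irrelevant one that differs by chance is included.

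Three further features make this worse:
- If the test ignores clustering, its true selection rate exceeds 1%.
- With nearly 20,000 patients, P<.01 is reached by very small differences, so the rule and the 0.1 yardstick disagree about which differences matter.
- Beyond the two named covariates, the content of model 2 is unknown until the arms are compared. This sits badly with a paper whose stated aim is to fix the methods before database lock.

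At stake is the value of model 2 as a robustness check. It may differ from model 1 for reasons unrelated to prognosis, and it gives up precision that balanced prognostic covariates could supply.

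**Working it through.** **Inputs from the SAP article.** 19,601 patients in 864 clusters (Participant Recruitment and Randomization), so 19,601/864 = 22.69 per cluster. Allocation 2:1, 576 and 288 clusters (Sample Size), so about 13,067 and 6,534 patients. Planning ICC 0.15, given for HbA1c control.

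**Assumptions.** The documents give no ICC for baseline variables; 0.02 to 0.15 is assumed. Allocation is treated as unstratified, and candidates as independent when the chance of at least one selection is computed.

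**1. Check of the design-effect formula against the plan's power.** DE = 1 + (19 − 1) × 0.15 = 3.70. Effective control size = 288 × 19/3.70 = 1,479, with twice that in the intervention arm. For 40% versus 45%, two-sided .05, power is 0.888 (0.890 with unpooled variance). The plan states 89%, so it is reproduced.

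**2. Smallest standardised difference reaching unclustered P<.01.**
2.576 × √(1/13,067 + 1/6,534) = 2.576 × 0.01515 = **0.039**.
With 19,008 patients it is 0.040, and with 16,416 it is 0.043. A difference of exactly 0.1 corresponds to z = 0.1/0.01515 = 6.6. This step does not depend on the ICC. Differences from about 0.04 to 0.10 are negligible by one section and trigger adjustment by the other.

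**3. True selection rate of the nominal 1% test.** DE = 1 + (22.69 − 1) × ICC; rate = 2 × [1 − Φ(2.576/√DE)].

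| Assumed ICC | DE | Selection rate | Expected selections among 18 | Chance of at least one |
|---|---|---|---|---|
| 0 | 1.00 | 1.0% | 0.18 | 17% |
| 0.02 | 1.43 | 3.2% | 0.57 | 44% |
| 0.05 | 2.08 | 7.4% | 1.34 | 75% |
| 0.15 | 4.25 | 21.2% | 3.81 | 99% |

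A simulation of 4,000 trials with 864 clusters of 22 gave 3.6%, 7.2% and 20.4% at ICC 0.02, 0.05 and 0.15; the formula at 22 per cluster gives 3.1%, 7.2% and 20.6%. Over this ICC range, more than 99% of chance selections have a standardised difference below 0.1.

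The 18 candidates are the variables in the cited list: age, sex, ethnicity; education, income, insurance; weight, BMI, waist, systolic and diastolic pressure; smoking; complications; HbA1c, FBG, LDL-C, creatinine; self-care score. For the primary outcome baseline HbA1c is already in model 1, which leaves 17 and 17 × 0.0315 = 0.5 to 17 × 0.2117 = 3.6 expected selections.

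**4. Would a clustered test be enough?** At ICC 0.15 the clustered threshold is 0.039 × √4.253 = 0.080, still below 0.1. Adjusting the test restores the 1% rate but not agreement with the yardstick, and it still does not select on prognosis.

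**The case against.** **The impact is limited.** Model 2 is a sensitivity analysis, and the shells of Tables 2 and 3 report only the primary model. The rule was written by authors blinded to allocation, so no analyst discretion is shown. A few extra baseline covariates in a trial of 864 clusters do not bias the effect. All of this stands. A reader might infer that the primary result is compromised or the effect estimate biased; the documents support neither.

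**The unclustered test is an inference.** Covariates-Adjusted Analyses names no test, the sentence on clustering sits beside standardised differences, and General Analysis Principles says that analyses adjust for clustering. This stands as a caveat. The cross-reference makes the unclustered reading the natural one, and step 4 shows that a clustered test would not cure the problem.

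**The inflation may be smaller.** The ICC of 0.15 is the planning value for HbA1c control, and the Discussion warns that it may differ here. Stratified allocation, which the text hints at, would shrink chance differences. This is why a range is given; 0.15 should not be read as the ICC of age, sex or smoking.

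**The two criteria serve different purposes.** The 0.1 describes Table 1, while P<.01 selects covariates. That is true, and no result depends on both. But one plan then calls a difference negligible and adjusts for it because of its size, and the Table 1 shell shows no P values from which a reader could see what drove the choice.

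**Diabetes duration is not barred.** A reader might infer that duration and baseline treatment can never be selected. The text does not say so: both sections introduce their variables with an open wording, and Table 1 lists duration. Only the weaker statement holds, that their eligibility is not fixed.

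**Conclusion.** The point holds as a defect in how a sensitivity model is specified. The firmest part needs no assumed ICC: clusters were randomised after baseline, so the rule responds to chance, and an unclustered P<.01 is reached at about 0.039, roughly two-fifths of the plan's 0.1. The inflated selection rate (about 3% to 21%, or 0.6 to 3.8 chance selections among 18 variables against 0.18) is conditional on an unclustered test, the assumed ICC range and unstratified allocation. Diabetes duration is in Table 1 but not in the cited list, and baseline glucose-lowering treatment is in neither, so whether they are candidates is left open. The loss of precision from omitting balanced prognostic covariates is real in principle but cannot be sized from the documents. Model 1 and the primary conclusion are not affected.

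**What to change.** Delete the P<.01 rule and state model 2 in full: baseline value of the outcome (as handled in model 1), economic development level, locality, age, sex, education, duration of diabetes and comorbidities. This is the covariate list of the propensity model under Comparison Between Basic and Intensive Intervention, and the same patient variables are in the imputation model. BMI and baseline insulin or oral drug use are optional additions; the documents give no data on how prognostic they are. Keep the standardised differences in Table 1 as description only.

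Table 2 adjusts for no baseline variable in the composite ABC outcome and only for systolic pressure in BP control, so the sentence should say whether model 2 follows suit.

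The cost is one sentence and a few more model terms, with no new data. Because the plan was signed off in November 2019, the change should be recorded as a dated amendment, and if it is made after the January 2020 lock it should be reported as such.

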#### Imputed Data Analyses

Multiple imputation using fully conditional specification [15] will be performed as a sensitivity analysis when more than 10% of observations in HbA_1c_ is missing at 1 year. The imputation model will include the levels of HbA_1c_, FBG, BP, and LDL-C at 1 year and at baseline; a cluster indicator; a group indicator; and other baseline variables including age, sex, education, duration of diabetes, comorbidities, economic development level, and locality (urban or rural). Ten sets of imputed data will be created and analyzed using the model 1 (described in “Primary Analyses”). HbA_1c_, FBG, BP, and LDL-C will first be imputed as continuous variables using linear regression and subsequently converted into binary variables. Estimates of the intervention effect after imputation (β in model 1) and its standard errors will be combined to obtain a pooled common RR and 95% CI.

#### Subgroup Analyses

Five prespecified subgroup analyses will be carried out between the overall intervention group and the control group. The subgroups are economic development level (developed vs less-developed), locality (urban vs rural), age group (<60 years of age vs ≥60 years of age), duration of diabetes (≥6 years vs <6 years, around the median), and diabetic complication (yes vs no; yes is defined as presence of any diagnosed diabetic nephropathy, diabetic retinopathy, peripheral neuropathy, carotid artery disease, lower extremity artery disease, diabetic foot damage, peripheral vascular disease, coronary stenosis, myocardial infarction, postcoronary artery surgery, cerebral infarction, or cerebral hemorrhage).

The analysis for each subgroup analysis will be performed by adding the subgroup variable along with its interaction with the intervention as fixed effects to the primary model (model 1). Within each subgroup, the raw counts and percentages within each treatment arm will be presented, as well as the RRs and their 95% CIs for the intervention effect from the primary model. The results will be displayed on a forest plot including the *P* value for heterogeneity corresponding to the interaction term between the intervention and the subgroup variable.

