### Analysis of the Primary Outcome

#### Primary Analyses

The primary endpoint, control rate of HbA_1c_ at 1 year, will be first compared between all intervention groups and all control groups. The primary analysis of the intervention effect will be conducted using a log-binomial regression with generalized estimating equations (GEE) to account for clustering within communities and with adjustment for baseline HbA_1c_ as a continuous covariate (model 1). The raw number and percentage of patients with adequate control of HbA_1c_ at 1 year will be reported. The effect of the intervention will be presented as the relative risk (RR) of the proportion of HbA_1c_ levels <7% along with its 95% CI and corresponding *P* value. In cases of a convergence issue, the logistic regression with GEE and the Poisson regression with GEE will be both used as the alternative methods, with the Poisson regression as the sensitivity analysis. The odds ratio along with the indirectly derived RR will be reported for the logistic regression.

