**Secondary outcomes**						
	FBG^d^ < 7.0 mmol/L		xxx (xx.x)	xxx (xx.x)	x.xx (x.xx-x.xx)	.xx
	BP^e^ < 140/80 mmHg^f^		xxx (xx.x)	xxx (xx.x)	x.xx (x.xx-x.xx)	.xx
	LDL-C^g^ < 2.6 mmol/L		xxx (xx.x)	xxx (xx.x)	x.xx (x.xx-x.xx)	.xx
	Composite diabetes control^h,i^		xxx (xx.x)	xxx (xx.x)	x.xx (x.xx-x.xx)	.xx

^a^Primary model: log-binomial regression with generalized estimating equation (GEE) with adjustment of the baseline value of the analyzed outcome and clustering. The logistic regression with GEE will be employed as the alternative method in case of non-convergence, with indirectly derived relative risk reported.

^b^RR: relative risk.

^c^HbA_1c_: glycated hemoglobin.

^d^FBG: fasting blood glucose.

^e^BP: blood pressure.

^f^Only systolic blood pressure at baseline and clustering were adjusted in the primary model for BP control.

^g^LDL-C: low-density lipoprotein cholesterol.

^h^Composite diabetes control: defined as HbA_1c_ level <7.0%, BP <140/80 mmHg and LDL-C <2.6 mmol/L.

^i^No baseline variable was adjusted in the primary model for the composite diabetes control.

**Table 3 table3:** Estimated effects of intervention compared to control on the change from baseline of continuous outcomes.

Secondary continuous outcome		Control, mean (SD)	Intervention, mean (SD)	Primary model^a^	
				Mean differences (95% CI)	*P* value

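### If a log-binomial subgroup model does not converge, the plan's lead fallback would place a test of equal odds ratios beside relative risks on the forest plot

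*SAP article*

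**What the plan says.** Three parts of the SAP article bear on this.

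- **Subgroup Analyses.** Each of the five subgroup variables and its interaction with the intervention is added to model 1, the log-binomial GEE. The forest plot shows "the RRs and their 95% CIs for the intervention effect from the primary model", together with a P "value for heterogeneity corresponding to the interaction term between the intervention and the subgroup variable". This section does not mention a fallback.
- **Primary Analyses.** "In cases of a convergence issue, the logistic regression with GEE and the Poisson regression with GEE will be both used as the alternative methods". Of the two, Poisson has the lesser role of a sensitivity check, so logistic leads. On reporting: "The odds ratio along with the indirectly derived RR will be reported for the logistic regression".
- **Table 2, footnote a.** "The logistic regression with GEE will be employed as the alternative method in case of non-convergence, with indirectly derived relative risk reported". Poisson is not named here.

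Analysis for Binary Categorical Outcomes extends a similar strategy, including subgroup analysis, to the binary secondary outcomes. Continuous outcomes use a linear model and hypoglycemia uses Poisson regression.

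**The concern.** In a log-link model the interaction coefficient is the log of the ratio of the two subgroup RRs, so its P value tests what the forest plot shows. In a logistic model the coefficient is the log of the ratio of the two ORs. Deriving an RR from the OR changes the displayed estimate but leaves the interaction coefficient, and hence its null hypothesis, on the OR scale. This holds even if every derived RR is correct.

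If control rates differ between subgroups, equal RRs and equal ORs cannot both hold once there is an effect. The trial could then report that the model of care works differently by age, diabetes duration or complication status although the plotted RRs are the same. It could also miss a real difference in RR. Each subgroup model is fitted separately, so one forest plot could mix RR-scale and OR-scale P values without saying so.

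**Working it through.** **Inputs from Sample Size.** 864 clusters (576 intervention, 288 control), 19 evaluable patients each, ICC 0.15, control rate 40%, absolute increase 5 points, two-sided 5%. Hence 5,472 control and 10,944 intervention patients, and RR = 0.45/0.40 = 1.125.

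**The plan's own figure.** Design effect = 1 + (19 − 1) × 0.15 = 3.7. Effective sizes are 5,472/3.7 = 1,479 and 10,944/3.7 = 2,958. SE = √(0.40 × 0.60/1,479 + 0.45 × 0.55/2,958) = 0.0157. Power = Φ(0.05/0.0157 − 1.96) = 89.0% (88.8% with pooled variance). The stated 89% is reproduced, so these inputs are a sound base.

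**Assumption.** The plan gives no control rates by subgroup. I take pairs centred on 40%, two equal-sized subgroups, and the same RR of 1.125 in both.

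**Scale mismatch.** OR = [1.125p/(1 − 1.125p)] / [p/(1 − p)]. At p = 0.30: (0.3375/0.6625)/(0.30/0.70) = 1.189. At p = 0.50: (0.5625/0.4375)/(0.50/0.50) = 1.286. The ratio of ORs is 1.08 although the ratio of RRs is exactly 1.

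**Rejection rate, Wald approximation.** With d the log ratio of the two ORs, Var(d) = D × Σ 1/[n q(1 − q)] over the four arm-by-subgroup cells. Here q is the cell's control rate and n its number of patients (2,736 control or 5,472 intervention). D = 1 approximates a patient-level subgroup, where the community effect largely cancels. D = 3.7 applies to a community-level subgroup. At 30%/50%, d = 0.0785. The SE is 0.0690 (patient level, z = 1.14) or 0.1327 (community level, z = 0.59).

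| Control rates | ORs at RR 1.125 | Patient-level rejection | Community-level rejection |
|---|---|---|---|
| 37%/43% | 1.214, 1.242 | 6.3% | 5.4% |
| 35%/45% | 1.206, 1.253 | 8.7% | 6.0% |
| 32%/48% | 1.195, 1.272 | 14.8% | 7.6% |
| 30%/50% | 1.189, 1.286 | 20.6% | 9.1% |

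**Simulation at the planned size, common RR 1.125.** Simulation A includes baseline HbA1c as a covariate (SD 1.6, logit slope −0.5 or −0.8 per 1%, both assumed) with 1,000 trials per setting. Simulation B omits the covariate and uses 800 trials per setting. Both use cluster-robust variance and apply both links to the same data.

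| Control rates | Subgroup level | Logistic, A | Logistic, B |
|---|---|---|---|
| 35%/45% | patient | 8.8-9.6% | 9.8% |
| 35%/45% | community | 6.9-7.0% | 6.0% |
| 30%/50% | patient | 22.9-26.6% | 20.8% |
| 30%/50% | community | 10.5-12.8% | 9.3% |

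The log-link interaction rejected in about 4-6% in every one of these settings.

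**Sensitivity.** At RR 1.25 and 30%/50%, the ORs are 1.40 and 1.67, and logistic rejection in simulation B is 27% (community) and 72% (patient). Unequal subgroups reduce the effect: at 32%/48%, patient level, the Wald figure falls from 14.8% with equal subgroups to about 11% with a 20:80 split.

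**The reverse error.** A common OR of (0.45/0.55)/(0.40/0.60) = 1.227 gives an RR of 1.149 at a 30% control rate and 1.102 at 50%. The logistic null is then true although the RRs differ.

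**The case against.** As written, Subgroup Analyses uses the log-binomial model for both the RRs and the interaction, so test and display agree. It names no fallback, and footnote a belongs to the table of overall effects. A reader might infer that the plan states a logistic test of heterogeneity. It does not: that follows only from reading the sections together, and only if a model fails to converge. This limit stands.

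Poisson GEE, which has a log link, is also planned on non-convergence, so an RR-scale interaction could be produced. That softens the point but does not remove it, because Poisson ranks below logistic and is not assigned the heterogeneity P.

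The subgroups are exploratory, and raw counts and percentages per arm appear beside the RRs, so a careful reader could see similar RRs behind a small P. That limits the harm. No null of equal RRs is written down either, and heterogeneity depends on the scale under any link. But once the plan displays RRs, a P on another scale needs at least a label, and the plan provides none.

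The size depends on assumed subgroup rates, and the probability of non-convergence is not estimated. A log link with continuous baseline HbA1c can push fitted probabilities above 1, and the plan provides for failure in two places, so the trigger is plausible but unquantified.

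A reader might also infer that every heterogeneity test in the plan is exposed. The continuous-outcome and hypoglycemia subgroup analyses are not, since neither relies on a logistic model.

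**Conclusion.** The point holds conditionally. The stated fallback, carried into the subgroup analyses, gives a heterogeneity P that does not test equality of the RRs beside it. At the planned RR of 1.125 and a nominal 5%, rejection under equal RRs is about 9-10% (35%/45%) to 21-27% (30%/50%) for age, duration and complications. For locality and economic level it is about 6-7% to 9-13%, a small inflation. With rates as close as 37%/43% it is negligible. These figures assume equal-sized subgroups and control rates that the plan does not give.

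The binary secondary outcomes share the issue. The main comparison of intervention with control is unaffected by this point, and so is any panel whose log-binomial model converges. It is a modest defect in how the fallback is ordered, worth correcting because the correction is nearly free.

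**What to change.** Add to Subgroup Analyses that, for any subgroup model in which the log-binomial GEE does not converge, both the subgroup RRs with their CIs and the heterogeneity P come from the log-link Poisson GEE with robust variance already listed in Primary Analyses. State that the logistic interaction P is not shown as the heterogeneity P on an RR forest plot. Apply the same rule to the binary secondary outcomes.

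Panels that converge can keep the log-binomial model, because both models work on the RR scale. Moving all five panels to Poisson would be a preference, not a need. A footnote should say which model each panel used.

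The cost is one or two sentences, a slight loss of efficiency in the affected panels, and a reversed order of the two planned fallbacks for subgroup analyses. Fixing this in advance also removes a post hoc choice between two P values.
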